**Secondary endpoints:**

*Quantitative measures of operational feasibility*

|        |                                                                                                                                                                                                                                                                                                                                                                                 |
|--------|---------------------------------------------------------------------------------------------------------------------------------------------------------------------------------------------------------------------------------------------------------------------------------------------------------------------------------------------------------------------------------|
| S2.SE1 | Proportion of health care practitioners who comply with the revised radical cure algorithm as defined below: 
 
Proportion of health care workers at the SCOPE health facility sites who correctly prescribe PQ (i.e. PQ7, PQ14 or PQ8W) according to the implementation package <math>\geq 95\%</math> of the time
 
              |
| S2.SE2 | Proportion of patients eligible for PQ who are tested for G6PD activity using the SD Biosensor at the time of their diagnosis of malaria.                                                                                                                                                                                                                                       |
| S2.SE3 | Proportion of eligible vivax malaria patients receiving the correct PQ regimen based on the result of the SD Biosensor test.                                                                                                                                                                                                                                                    |
| S2.SE4 | Proportion of vivax malaria patients who are ineligible for daily primaquine and are incorrectly prescribed an inappropriate primaquine regimen. 
Ineligible being defined as:
 
 
Infant <6 months or <5kg weight (Indonesia) or <1 year (PNG), pregnant women or women breastfeeding infants <6 months of age
 
 |

(Indonesia) or <1 year of age in PNG. Should not receive any primaquine

- G6PD deficient (<30% enzyme activity). Should not receive daily primaquine.

S2.SE5 Proportion of vivax malaria patients that are reviewed on day 3.

S2.SE6 Proportion of vivax malaria patients that adhere to their prescribed primaquine regimen defined as follows:

- The proportion of patients who self-report that they have taken all prescribed PQ doses between the time of the initial prescription and the follow-up visit.

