| PQ             | Primaquine                                                             |
| PQ7            | Primaquine 1.0 mg/kg/day for 7 days                                    |
| PQ14           | Primaquine 0.5 mg/kg/day for 14 days                                   |
| PQ8W           | Primaquine 0.75mg/kg/week for 8 weeks                                  |
| RDT            | Rapid Diagnostic Test                                                  |
| SAE            | Serious Adverse Event                                                  |
| SCOPE          | Short Course Primaquine for the radical cure of P. vivax |
| SMC            | Safety Monitoring Committee                                            |
| SRT            | Safety Review Team                                                     |

YPKMP

*Yayasan Pengembangan Kesehatan dan Masyarakat Papua*  
(Papua Health and Community Development Foundation)

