## 1 INTRODUCTION

### 1.1 Preface

Outside of sub-Saharan Africa, *Plasmodium vivax* is becoming the predominant cause of malaria. Although prevention of relapses is crucial for reducing transmission of this important disease, only two drugs (primaquine and tafenoquine) are licensed for treatment of hypnozoites (the latent liver stages) of *P. vivax* and thus have potential to prevent relapses. Primaquine is the anti-relapse drug available in most endemic regions, but its widespread impact on health outcomes is limited by poor adherence to the standard 14-day course and concerns over the risk of drug-induced haemolysis in patients with glucose-6-phosphate dehydrogenase (G6PD) deficiency. Over the last few years, new tools and treatment strategies have been developed for better tolerated and more effective radical cure regimens. Short-course (7 days), high daily-dose primaquine has been shown to have similar efficacy compared with the same WHO-recommended total dose of 7mg/kg body weight administered over 14 days (Taylor W.J. et al. 2019) in areas with high risk of relapse. However, the higher daily dose in the 7 day regimen (1mg/kg) is associated with more adverse events, particularly an increased risk of haemolysis and gastrointestinal events. A semi-quantitative point-of-care G6PD test (SD Biosensor, ROK) has been developed and registered in Indonesia and the process of registration is underway in Papua New Guinea (PNG).

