### 1.2 Purpose of the analyses

The aim of the SCOPE study is to determine the effectiveness and safety of introducing a revised case management package to facilitate well-tolerated and effective radical cure of patients with vivax malaria at 10 public health care facilities in Indonesia and Papua New Guinea.

The revised case management package has been prioritised and endorsed by the respective Ministries of Health and will include: 1) semi-quantitative point-of-care glucose-6-phosphate dehydrogenase (G6PD) activity assessment prior to treatment with primaquine, 2) prescription of high dose (7mg/kg body weight total) primaquine over 7 (**PQ7**), 14 (**PQ14**) days or 8 weeks (**PQ8W**), to all eligible patients presenting with *P. vivax* malaria, 3) patient education and counselling prior to treatment and supervision of the first dose of primaquine at the health care facility, 4) community-based clinical review at day 3 of primaquine treatment to encourage treatment adherence and facilitate detection and management of adverse events to treatment and 5) improved malariometric surveillance and pharmacovigilance.

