### Secondary objectives:

#### *Quantitative measures of operational feasibility*

- S2.SO1 Determine the proportion of health care practitioners who comply with the revised radical cure treatment algorithm
- S2.SO2 Determine the proportion of patients receiving a SD Biosensor G6PD test
- S2.SO3 Determine primaquine dosing accuracy by G6PD activity category
- S2.SO4 Determine the proportion of vivax malaria patients who are ineligible for daily primaquine and are incorrectly given primaquine (including infants, pregnant females and G6PD deficient patients)
- S2.SO5 Determine the proportion of vivax malaria patients that are reviewed on day 3
- S2.SO6 Determine the proportion of vivax malaria patients that adhere to their prescribed primaquine regimen

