### 3.1.2. Stage 2 – Large-scale implementation and feasibility study

Stage 2 of the study will be a feasibility study conducted at 10 community health-care facilities: 6 sites in Indonesia and 4 sites in Papua New Guinea. The primary purpose of Stage 2 is to determine the feasibility and cost-effectiveness of the complete revised case management initially studied in Stage 1. Robust Pre-Implementation malarimetric surveillance for a minimum of 12 months along with quantitative surveys of baseline operational metrics and costs will be followed by coordinated introduction of the revised case management across all study health facilities and a minimum of a further 12 months of surveillance – creating an interrupted time series comparing the endpoints listed in section 2.2.2.

During Stage 2 study procedures will be the same as those for Stage 1, except that the procedures will be performed by routine healthcare staff. All patients will be reviewed by community health workers (CHW) at home 3 days after starting PQ. The review may also take place at the health facility, if the patient presents there. Exceptionally, the follow-up may also take place via a phone call if the patient is not physically reachable at home. The CHW will complete a signs and symptom checklist to detect early indicators of haemolysis or other AESI. Patients with signs of haemolysis or other AESI will have their primaquine ceased and will be referred to the health facility for medical review. Patients tolerating their medication will be encouraged to adhere to a full (7 or 14 days) course of treatment. Safety outcomes occurring between day 3 and end of treatment will be detected passively by community-based health workers, study health facilities and regional hospitals.

Continuous surveillance and pharmacovigilance over the entire study period will enable interrupted time-series analyses of malarimetric indices (see section 2.2.2).

Figure 1 presents the study schedule for the baseline data, pre-implementation stage, and stages 1 and 2.

**Figure 1. Study overview**[figure not shown]

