### 3.2 Inclusion and exclusion criteria

**Inclusion criteria Stage 1 of the study (and thus receipt of either PQ7, PQ14 or PQ8w) are:** age >1 year (PNG) or ≥6 months (Indonesia), haemoglobin concentration ≥8 g/dl and signed agreement of patient or their carers to participate in the study and comply with all study-specific obligations, including attending follow-up clinical evaluations (at day 3 and day 7). Inclusion criteria for Stage 2 will be the same except that patients will only need to be able to attend a follow-up appointment (or receive a phone call) on day 3.

**Exclusion criteria:** pregnant and lactating females with infants <6 months in Indonesia and <1 year in PNG and patients with severe manifestations of malaria will not be prescribed primaquine and will not be enrolled in Stage 1. These patients will contribute incidence data to Stage 2 of the study but will not receive primaquine treatment. Patients' ineligible for primaquine treatment will be treated according to current national guidelines.

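### S2.SE6 is labelled adherence to the prescribed primaquine regimen, but it stops counting at the day-3 review, before any regimen is complete

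*SAP*

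**What the plan says.** In Section 2.1.2, objective S2.SO6 reads: "Determine the proportion of vivax malaria patients that adhere to their prescribed primaquine regimen". Section 2.2.2 repeats that aim in the stem of S2.SE6 and then gives the operational definition: "The proportion of patients who self-report that they have taken all prescribed PQ doses between the time of the initial prescription and the follow-up visit". The definition does not name the day of the visit.

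Sections 3.1.2 and 3.2 supply the timing:

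- Section 3.1.2: "All patients will be reviewed by community health workers (CHW) at home 3 days after starting PQ".
- Section 3.2, on how Stage 2 inclusion differs from Stage 1: "patients will only need to be able to attend a follow-up appointment (or receive a phone call) on day 3".
- Section 3.1.2, on the time after that review: "Safety outcomes occurring between day 3 and end of treatment will be detected passively by community-based health workers, study health facilities and regional hospitals".

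Table S1a in Appendix 3, the Stage 2 deviation table, treats a review on days 3-5 as the day-3 review. It also has a row for a missed day-7 review (days 6-10), which the Stage 2 design text does not schedule. Section 6.2 lists PQ7, PQ14 and PQ8W among the subgroups for patient-related outcomes.

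**The concern.** The label and the measurement cover different periods. The regimens last 7 days, 14 days or 8 weeks, while the count ends at a visit about 3 days in. A patient who takes every dose up to that visit and none afterwards is scored as adherent to the regimen.

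This matters because the motivation in Section 1.1 is about finishing a long course: primaquine is described as a drug for which "its widespread impact on health outcomes is limited by poor adherence to the standard 14-day course". Sections 1.2 and 3.1.2 also make the day-3 review the occasion on which patients are encouraged to continue. S2.SE6 is read at that moment, so it cannot register whether the encouragement worked.

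Followed as written, the report would carry a figure named regimen adherence that describes only the opening doses. The subgroup display would set three different fractions of a course side by side under one name.

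**Working it through.** The SAP gives no expected value, precision or power for S2.SE6, so there is no stated figure to reproduce. The check is a count of doses due, followed by an illustration.

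**Inputs**

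- PQ7: "Primaquine 1.0 mg/kg/day for 7 days" (List of Acronyms), so 7 daily doses.
- PQ14: 14 daily doses; PQ8W: 8 weekly doses (same list).
- Visit: day 3 (Sections 3.1.2 and 3.2), window day 3-5 (Table S1a).
- First dose: the package includes "supervision of the first dose of primaquine at the health care facility" (Section 1.2). I count it as day 0.

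**Doses due at the review, divided by doses in the course**

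The lowest count is a day-3 visit with that day's dose not counted (days 0-2, 3 doses). The highest is a day-5 visit with that day's dose counted (days 0-5, 6 doses).

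- PQ7: 3/7 = 42.9% to 6/7 = 85.7%.
- PQ14: 3/14 = 21.4% to 6/14 = 42.9%.
- PQ8W: 1/8 = 12.5% throughout, because the second weekly dose falls on day 7. The one dose due is the dose that the package supervises.

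No regimen is complete anywhere in the window. A visit on days 6-10, as in the extra row of Table S1a, could cover PQ7, but would reach at most 11 of 14 PQ14 doses (days 0-10) and 2 of 8 PQ8W doses.

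**Illustration**

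Assume that the first dose is supervised and that there is a constant chance *d* of stopping before each later dose. The SAP does not give *d*. The probability of having taken *k* doses is (1 − *d*)^(*k* − 1). The exponents are 2 and 5 for S2.SE6 with 3 and 6 daily doses due, 6 for the PQ7 course and 13 for the PQ14 course.

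| *d* | S2.SE6, 3 doses due | S2.SE6, 6 doses due | PQ7 completed | PQ14 completed |
|---|---|---|---|---|
| 2% | 96% | 90% | 89% | 77% |
| 5% | 90% | 77% | 74% | 51% |
| 10% | 81% | 59% | 53% | 25% |

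At *d* = 5%, S2.SE6 exceeds completion as follows:

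- PQ7: from 90.2 − 73.5, about 17 points, down to 77.4 − 73.5, about 4 points.
- PQ14: from 90.2 − 51.3, about 39 points, down to 77.4 − 51.3, about 26 points.

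With equal *d* and the same visit day, S2.SE6 is identical for PQ7 and PQ14 whatever their completion. For PQ8W it is 100% when the first dose was supervised, against 0.95^7 = 70% over the eight weeks.

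**The case against.** The best defence is that the definition is open about what it counts, and that intake up to an early visit is a legitimate and feasible measure in routine care. That stands. The fault lies in the name and in the conclusion that the name invites.

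It can also be said that S2.SE6 never says day 3, and that Table S1a has a day-7 row. Day 3 is an inference, but a firm one: the Stage 2 text schedules no other visit and describes only passive safety detection afterwards. The day-7 row also stands in Table S1 for Stage 1 and looks carried over. It would not rescue the label for PQ14 or PQ8W in any case.

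Some stronger readings are tempting and are not supported:

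- *PQ8W patients materially inflate the pooled figure.* Section 4.1 assumes that 764 of 800 Stage 1 patients qualify for PQ7, leaving 36/800 = 4.5% for PQ14 and PQ8W together. Carry that mix into Stage 2 and suppose all 4.5% were PQ8W at 100%. At *d* = 5% the pooled figure would rise by 0.045 × (100 − 90), about 0.4 points, or 0.045 × (100 − 77), about 1 point at the late edge of the window. Section 3.1.1 anticipates 700 on PQ7 and 100 on PQ14, which leaves nobody on PQ8W.
- *S2.SE6 cannot fail for PQ8W.* That requires the first dose to have been supervised. Appendix 1 has variables for whether it was observed and why not, so failures are possible.
- *A planned PQ7-versus-PQ14 adherence comparison fails.* None is planned. Section 9.2 gives proportions with binomial intervals, overall and by country and facility, and Section 6.2 is a general subgroup list. Regimen follows G6PD activity, so such a contrast would be confounded anyway.
- *Stage 2 holds no information on completion at all.* The protocol and the separate document on qualitative feasibility measures (Section 2.1) are not at hand, so only S2.SE6 itself can be judged.

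S2.SE6 is one of 18 secondary endpoints and is not a component of S2.PE1, which limits the consequences.

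**Conclusion.** The point holds as a mismatch between label and measurement. S2.SO6 and S2.SE6 promise adherence to the regimen; the definition delivers self-reported intake over the first 3 to 6 daily doses, or the first weekly dose. The fraction of the course covered is 43-86% for PQ7, 21-43% for PQ14 and 12.5% for PQ8W, so the subgroup figures do not describe the same thing.

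The dose counts rest on the first dose being day 0 and on the day 3-5 window. The size of the overstatement rests on an assumed stopping rate: at 5% per dose it is about 4 to 17 points for PQ7 and 26 to 39 points for PQ14. That S2.SE6 cannot fall below completion does not depend on the rate, since a completed course includes the doses due by the review. The matter deserves correction because it changes what may be concluded about adherence, but it does not touch the primary endpoint.

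**What to change.** - Rename S2.SO6 and S2.SE6 as self-reported intake of all primaquine doses due by the day-3 review (early adherence), and name the visit and its window in the definition.
- Report the result by regimen, with the number of doses due at the review beside each figure.
- Add a table footnote saying that S2.SE6 does not estimate course completion and is not to be compared across PQ7, PQ14 and PQ8W as if it did.
- Reconcile the day-7 review row in Table S1a with the Stage 2 design in Sections 3.1.2 and 3.2.
- Optionally, because Section 8 analyses available cases only, add a lower bound that counts patients without a day-3 review as non-adherent.

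The cost is SAP wording and one footnote. No visit, data item or clinical procedure changes. The price is a more modest adherence claim.

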#### *Pharmacovigilance*

S2.SE7 Proportion of CHWs who correctly act on early signs of haemolytic anaemia and GI events defined as follows:

- Proportion of CHWs who refer 100% of patients documented as having a potential severe symptom ('flag') at day 3 review for level 2 clinical review
- Proportion of patients with a severe symptom ('flag') at day 3 review who are referred by a CHW for level 2 review

S2.SE8 Number of patients with a SAE who are identified by community or health facility staff follow-up and referred to hospital for further management.

#### *Safety*

S2.SE9 The proportion of patients eligible to receive PQ who had a serious adverse event (SAE) during treatment.

S2.SE10 The proportion of patients treated with PQ experiencing at least one AESI during treatment.

S2.SE11 The proportion of patients treated with PQ with an AESI related to haemolysis during treatment.

S2.SE12 The proportion of patients treated with PQ with a gastrointestinal AESI during treatment.

S2.SE13 The proportion of patients treated with PQ with AESI related to methaemoglobinaemia during treatment.

S2.SE14 Prevalence of severe anaemia (haemoglobin < 7g/dl) in patients presenting with fever in the Pre-Implementation Survey versus the late Post-implementation Survey (derived from the quantitative surveys).

- Median and distribution of haemoglobin concentrations will also be presented for each survey

*Effectiveness*

- S2.SE15 The monthly incidence of confirmed symptomatic *P. vivax* malaria episodes (mono-infection or mixed) in the Pre-Implementation (12 months) versus Post-Implementation Stage 2 ((a) level change in 6 months post implementation (i.e. period between 6 and 12 months post-implementation), (b) change in trend of incidence immediately post-implementation (i.e. entire 12 month period post-implementation)).
- S2.SE16 Prevalence of *P. vivax* parasitaemia in patients presenting with fever in the Pre-Implementation Survey versus the Post-Implementation Survey during Stage 2 (derived from the quantitative surveys).
- S2.SE17 Cumulative risk of representation to the same health facility with symptomatic *P. vivax* malaria within 6 months in the Pre- and Post-Implementation Stages.
- S2.SE18 Cumulative risk of representation to the same health facility with symptomatic *P. vivax* malaria within 6 months in the Post-Implementation Stage for patients enrolled and not enrolled in SCOPE.

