#### *Safety*

- S2.SO9 Determine the safety of PQ under real-world conditions
- S2.SO10 Determine the risk of patients experiencing at least one AESI during treatment
- S2.SO11 Determine the risk of patients experiencing severe haemolysis AESI during treatment
- S2.SO12 Determine the risk of patients experiencing severe GI AESI during treatment
- S2.SO13 Determine the risk of patients experiencing severe methaemoglobinaemia AESI during treatment
- S2.SO14 Determine the difference in severe anaemia prevalence between the pre- and post-implementation periods of the revised case management

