## 2.2 Endpoints

### 2.2.1. Stage 1 – Preliminary safety and feasibility study

All endpoints refer to patients enrolled into Stage 1 treated with daily or weekly PQ.

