|                                                                                                        | N=      | N=  | N=  | N=  | N=  | N=  | N=  | N=  | N=  | N=  | N=   |
| PRESCRIBING DEVIATIONS                                                                          |         |     |     |     |     |     |     |     |     |     |      |
| Pregnancy n (% of all female patients)                                                          |         |     |     |     |     |     |     |     |     |     |      |
| Treated with PQ                                                                                        |         |     |     |     |     |     |     |     |     |     |      |
| Breast Feeding infants (<6 months Indonesia, <12 months PNG) n (% of all female patients) |         |     |     |     |     |     |     |     |     |     |      |
| Treated with PQ                                                                                        |         |     |     |     |     |     |     |     |     |     |      |
| Age <1year (PNG), <6 months (Indonesia) n (% of all enrolled pts)                         |         |     |     |     |     |     |     |     |     |     |      |
| Treated with PQ                                                                                        |         |     |     |     |     |     |     |     |     |     |      |
| Patients with Pf (Mono) n (% of all enrolled pts)                                               |         |     |     |     |     |     |     |     |     |     |      |
| Treated with PQ                                                                                        |         |     |     |     |     |     |     |     |     |     |      |
|                                                                                                        |         |     |     |     |     |     |     |     |     |     |      |
| G6PD normal >70% N(% of all enrolled pts)                                                    |         |     |     |     |     |     |     |     |     |     |      |
| Treated with PQ14 n(%)                                                                                 |         |     |     |     |     |     |     |     |     |     |      |
| Treated with PQ8W n(%)                                                                                 |         |     |     |     |     |     |     |     |     |     |      |

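### S2.SE9 measures the safety of primaquine among patients eligible for it, not patients treated with it, so SAEs in patients given it in error fall outside the proportion

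*SAP*

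**What the plan says.** Section 2.2.2 of the SAP defines S2.SE9 as "The proportion of patients eligible to receive PQ who had a serious adverse event (SAE) during treatment". It serves objective S2.SO9 in section 2.1.2: "Determine the safety of PQ under real-world conditions".

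The endpoint listed next, S2.SE10, is "The proportion of patients treated with PQ experiencing at least one AESI during treatment", and S2.SE11 to S2.SE13 also use patients treated with PQ. For Stage 1, section 2.2.1 states: "All endpoints refer to patients enrolled into Stage 1 treated with daily or weekly PQ". That covers the matching SAE endpoint, S1.PE1.

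The plan treats eligibility and treatment as different things. S2.SO4 concerns patients "ineligible for daily primaquine and are incorrectly given primaquine (including infants, pregnant females and G6PD deficient patients"), and S2.SE4 measures the "Proportion of vivax malaria patients who are ineligible for daily primaquine and are incorrectly prescribed an inappropriate primaquine regimen". Dummy Table S1a in Appendix 3, on Stage 2 protocol deviations, has a heading "Pregnancy n (% of all female patients") with a row beneath for those treated with PQ. It has similar rows for breastfeeding women and under-age children.

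Section 6.2 bases the Stage 2 analyses on all enrolled patients and defines no safety set. Section 9.2 names no population for S2.SE9. The precision statement headed S2.SE9 in section 4.2.1 uses n = 11,410, a number that the same section, under S2.SE15, describes as patients receiving primaquine.

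**The concern.** An endpoint on the safety of a drug needs the people exposed to the drug as its population. S2.SE9 uses a different group, and the mismatch works in two directions.

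- **Exposed but not eligible.** A pregnant woman, a woman breastfeeding a young infant, or an infant below the age limit who is given PQ in error and has an SAE is outside both numerator and denominator. If the SAE is not also an AESI, it enters none of the proportions S2.SE9 to S2.SE13.
- **Eligible but not exposed.** An eligible patient who takes no PQ is in the denominator, yet cannot contribute an event during treatment.

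In Stage 2 the package is run by routine staff, so SAEs after mis-prescription bear directly on the real-world safety question. SAEs are likely to be few, so even one or two such cases matter to the reader of the safety table. Without a stated safety set, analysts could also use enrolled, eligible or treated patients and each claim to follow the plan.

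**Working it through.** **1. The plan's own figure.** Section 4.2.1 gives +/- 0.18% for a 1% event proportion with n = 11,410. The normal-approximation half-width is

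1.96 x sqrt(0.01 x 0.99 / 11,410) = 0.183%.

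The figure reproduces. The 1% there refers to treatment-limiting haemolytic events, not SAEs, so it is used below only as a convenient reference risk. Because 11,410 is described as the number receiving PQ, the calculation already rests on a treated count, while the definition says eligible.

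**2. Populations side by side.**

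| Endpoint | Population |
|---|---|
| S1.PE1 (SAE, Stage 1) | treated with daily or weekly PQ |
| S2.SE9 (SAE, Stage 2) | eligible to receive PQ |
| S2.SE10 to S2.SE13 (AESIs, Stage 2) | treated with PQ |

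**3. SAEs left out.** Table 1 of the SAP gives 17,160 *P. vivax* episodes a year and a maximum recruitment of 16,302, so 17,160 - 16,302 = 858 are ineligible. The SAP gives neither the share of these given PQ in error nor their SAE risk. Both are assumed here to lie between 1% and 10%.

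- Low end: 858 x 0.01 = 8.6 patients exposed; 8.6 x 0.01 = 0.09, about 0.1 SAE omitted.
- High end: 858 x 0.10 = 85.8 patients exposed; 85.8 x 0.10 = 8.6 SAEs omitted.

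Against a reference of 114.1 SAEs (an assumed 1% of 11,410), the omitted share of all on-treatment SAEs runs from 0.09 / 114.2 = 0.1% to 8.6 / 122.7 = 7%. At the high end the proportion among all treated patients would be (114.1 + 8.6) / (11,410 + 85.8) = 1.07%, against 1.00% as S2.SE9 is written. If the wrongly treated have the same 1% risk as the rest, both proportions are 1.00% and only the count changes.

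**4. Dilution.** If a share u of enrolled eligible patients takes no PQ, the reported proportion is the true proportion x (1 - u). For u from 1% to 10% (assumption), a true 1.00% reads 0.99% to 0.90%.

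**5. Precision after the change.** With a treated denominator of 11,410 the half-width is that of step 1, 0.18%.

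**The case against.** The best defence is that in this study eligible and treated patients nearly coincide. Section 3.2 links meeting the inclusion criteria to receipt of PQ, section 6.2 restricts the analysis to enrolled patients, and sections 9.2 and 11 use eligibility for PQ as shorthand for a population. This stands as an argument that dilution is probably small. It also disposes of a stronger reading, that a true 1.00% would appear as 0.70%: that requires all 16,300 eligible patients in the denominator with only 11,410 treated, including people never enrolled.

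A reader might further infer that a large part of the SAEs disappears, for example 2 of 13 (15%). Such a figure could come from 11 SAEs in 11,410 eligible patients and 2 in 43 wrongly treated ones. It needs an SAE risk of 4.65% against 0.096%, about 48 times higher, and the SAP supports no such ratio. At equal risk, 43 patients would yield 0.04 SAEs.

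Nor does the exclusion necessarily lower the reported proportion. It does so only if wrongly treated patients have a higher SAE risk than the others. The SAP has no figure on this.

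It would also go too far to say that S2.SE9 drops everyone who should not have had the regimen they received. Patients with G6PD activity below 30% are ineligible only for daily PQ, so one wrongly given daily PQ may still count as eligible; the text does not say.

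The events are not lost to all reporting either. S2.SE8 counts SAE patients without an eligibility limit, S2.SE10 to S2.SE13 include serious AESIs in all treated patients, and S2.SE4 and Table S1a show who was wrongly treated. This cover is partial: S2.SE8 has no denominator and requires referral to hospital, and S2.SE10 to S2.SE13 miss SAEs that are not AESIs.

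Finally, the SAP plans no formal comparison of S2.SE9 with S1.PE1, so a broken comparison is not the main harm.

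None of this repairs the definition. It limits the size of the consequence.

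**Conclusion.** The point holds as a wrong population for one descriptive secondary endpoint. As written, S2.SE9 does not measure what S2.SO9 asks, differs without explanation from S2.SE10 to S2.SE13 and S1.PE1, and disagrees with the treated count behind its own precision statement. It leaves out SAEs in a group that the plan itself expects to exist.

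The numerical effect is unknown and probably small. The ranges of 0.1 to 8.6 omitted SAEs and 0.99% to 0.90% for a true 1.00% rest on assumed mis-prescription, SAE and non-treatment rates. The 858 is a yearly count of presentations; how many of them would enter the Stage 2 dataset is not stated. A substantial or one-directional understatement of the SAE proportion cannot be concluded from the SAP.

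Severity is moderate. S2.SE9 carries no hypothesis test, and the SAP attaches no Stage 2 decision rule to it.

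**What to change.** - Redefine S2.SE9 as the proportion of patients who received at least one dose of PQ, regardless of eligibility, who had an SAE during treatment. State this population in section 6.2 as the safety set for S2.SE9 to S2.SE13.
- Add a separate row for ineligible patients who received PQ, giving SAE counts and the denominator.
- State in which row patients with G6PD activity below 30% who were given daily PQ are reported.

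The cost is SAP wording and one table row. Appendix 1 already lists the variables for SAEs, pregnancy, lactation, age, G6PD activity and PQ treatment. The precision of +/- 0.18% at n = 11,410 is unchanged.
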